### **5.13 Other Events Requiring Immediate Reporting**

The investigator must report the following events by emailing or faxing the appropriate form to the local medical monitor within 24 hours of becoming aware of the event:

- Withdrawal of consent during the study due to an adverse event (Immediately Reportable Event Form)
- Emergency unblinding (Immediately Reportable Event Form)
- Protocol deviation affecting the safety of a subject or involving the vaccination process (Immediately Reportable Event Form)

- Adverse event thought to be an allergic reaction to the study vaccine (Immediately Reportable Event Form, unless event meets SAE criteria)
- Any event that, in the opinion of the investigator, precludes further administration of the study vaccine (Immediately Reportable Event Form, unless meets SAE criteria)
- Pregnancy (Pregnancy Notification Form)

#### **5.14 Adverse Event Treatment, Follow-up, and Outcome**

Treatment of any adverse events will be determined by the investigator using his/her best medical judgment and according to current clinical practice guidelines. All applied measures as well as follow-up will be recorded on the appropriate screen.

Adverse events will be considered resolved when the condition returns to normal or returns to the subject's baseline status as established on Study Day 0, or when the condition has stabilized with the expectation that it will remain chronic.

The investigator will continue follow-up on adverse events, including laboratory abnormalities and solicited adverse events, until the event has resolved, is otherwise satisfactorily explained, or the subject completes the study. If not reported earlier, the outcome of adverse events and solicited adverse events will be determined at the end of the specified post-vaccination adverse event reporting period.

Follow-up for serious adverse events must continue until resolution and the outcome reported to Aeras, even if this extends beyond the serious adverse event reporting period (i.e., after the final study visit). For analysis purposes, the outcome for serious adverse events will be determined on the final study visit.

Outcome of all adverse events will be classified as one of the following:

- Resolved
- Resolved with sequelae
- Ongoing
- Death

If at any time after completion of the serious adverse event reporting period (the final study visit) the investigator becomes aware of a serious adverse event that is suspected by the investigator to be related to the study vaccine, the event must be reported to Aeras.

#### **5.15 Follow-up of Subjects Who Become Pregnant**

If a subject becomes pregnant during the study, she should be encouraged to continue in the study for safety follow-up and for TB disease according to the protocol. Follow-up should continue for pregnancy outcome including premature terminations, and data are to be included in the safety reports.

The investigator must notify the local medical monitor, World Wide Safety Center and CRO, Triclinium, of the pregnancy immediately (even if already known to have resulted in

spontaneous or elective abortion) by emailing/faxing the Pregnancy Form to the medical monitor. At a minimum, the estimated date of conception, the estimated due date, and the date the subject received the study vaccine should be provided.

If a subject becomes pregnant, she will not have blood drawn as normally mandated by the protocol. The subject will undergo all other evaluations according to the Summary Schedule(s) of Evaluations.

The health status of the mother and child, the date of delivery, and the child's sex, birth weight and multiparity should be reported to the safety monitor after delivery. If delivery occurs before the final study visit, the subject should continue to be followed for SAEs through the final study visit unless withdrawal of consent has occurred. If delivery occurs after the final study visit, the investigator should attempt to maintain contact with the subject to obtain information after delivery.

Pregnancy will not be recorded as an adverse event. However, pregnancies will be recorded in the World Wide Safety Database. If the pregnancy results in a miscarriage, the event (spontaneous abortion) will be reported as an adverse event or a serious adverse event per the investigator's judgment (e.g., if it was a medically important or life-threatening event that meets the definition of a serious adverse event).

A congenital anomaly or birth defect (i.e., an adverse finding in a child or fetus of a subject exposed to the study vaccine before conception or during pregnancy) must be reported as a serious adverse event.

If it is determined after completion of the study that a subject became pregnant during the study, the subject should notify the investigator. The pregnancy must be reported to the local medical monitor and the status of the mother and child after delivery will be obtained and reported, when possible.

## **6 STOPPING RULES**

These rules govern the stopping of study vaccine administration at any time during the study. Stopping rules will include:

- Death in any subject that the DMC determines is RELATED to MVA85A/AERAS-485
- An anaphylactic reaction to MVA85A/AERAS-485 in any subject
- A life-threatening adverse event in any subject that the DMC determines is RELATED to MVA85A/AERAS-485
- A serious adverse event that the DMC determines is RELATED to MVA85A/AERAS-485
- A pattern of significant symptoms, physical findings or laboratory abnormalities (adverse events) that, although individually minor, collectively represent a safety concern in the opinion of the investigator or the medical monitor and that the DMC determines are RELATED to MVA85A/AERAS-485

The DMC may permit resumption of study vaccine administration if the study pause was for reasons less severe than those in the DMC stopping rules. The DMC may permit resumption of enrollment if it judges that changes to the study protocol will eliminate or greatly reduce the safety risks specified in the stopping rules. In the absence of study protocol changes the DMC must follow the DMC study stopping rules.

If a decision to resume study enrollment and study vaccine administration is made the DMC will record their judgment in a memorandum to the study file and notify the sponsor, who will then forward the DMC memorandum to the medical monitors and principal investigators. The clinical site will be allowed to resume activities upon receipt of written notification from the sponsor. The appropriate regulatory authority will be informed in writing if the study is stopped and will be informed in writing of the decision by the DMC to resume or discontinue study activities.

## **7 STATISTICAL CONSIDERATIONS**

The planned statistical analyses for this study are outlined below. A detailed statistical analysis plan will be created and finalized prior to database lock and preparation of any blinded preliminary data reviews and for preparation of the final study report (see Section 7.10).

### **7.1 Subject Populations**

The following population definitions will be utilized in specific analyses, as described below. The randomized subject population will consist of all subjects who were randomized into the study. The safety population will consist of all randomized subjects who received at least one dose of study vaccine. The per-protocol (PP) population for efficacy analyses will consist of all randomized subjects that received study vaccine and had no major protocol deviations, to be defined in the statistical analysis plan prior to database lock and study unblinding. The intent-to-treat (ITT) population for efficacy analyses will consist of all randomized subjects; given the proximity of randomization with vaccination, ITT as defined is anticipated to preserve the principles of ITT and to protect the randomization.

### **7.2 Demographics and Protocol Compliance**

Demographic parameters (age, gender, and race/ethnicity) and other baseline characteristics will be summarized by ART strata as defined in Section 3.3 and by treatment group for the safety population and for the PP population. Additional summaries based on all randomized subjects, and by ART strata and by study site, will also be provided.

Listings of randomized subjects who did not receive study vaccine or placebo, subjects who were excluded from the ITT or PP populations will be provided. The number (percentage) of subjects with protocol deviations (to be defined in the statistical analysis plan) will be summarized by treatment group, ART strata, and for all subjects in the ITT population.

## 7.3 Efficacy Analyses

### 7.3.1 Case Definition of Tuberculosis

A case of tuberculosis will be defined as any of the following:

#### **TB Case Definition Endpoint #1**

Any of the following numerical categories:

1. Isolation of *M. tuberculosis* from any site.
2. Identification of *M. tuberculosis* by an approved molecular diagnostic technique from any site.
3. Histopathology diagnostic for tuberculosis disease (such as caseating granulomas).
4. Choroidal tubercle diagnosed by ophthalmologist.

#### **TB Case Definition Endpoint #2**

Any of the following numerical categories:

1. Isolation of *M. tuberculosis* from any site.
2. Identification of *M. tuberculosis* by an approved molecular diagnostic technique from any site.
3. Histopathology diagnostic for tuberculosis disease (such as caseating granulomas).
4. Choroidal tubercle diagnosed by ophthalmologist.
5. A single smear/histology specimen positive for acid-fast bacilli from a normally sterile body site.
6. Two acid-fast smears positive each from a separate collection morphologically consistent with mycobacteria from either pulmonary or gastric sampling that are not found to be non-tuberculous mycobacteria bacteria on culture, and at least one of the following:
  - a) a compatible radiographic feature: airspace opacification, cavity, hilar or mediastinal adenopathy, or pleural effusion
  - b) a compatible clinical feature, i.e., more than 2 weeks of fever, night sweats, anorexia, cough, or weight loss (at least 5 kg by history or noticeable change in clothing fit); or one or more episodes of hemoptysis.

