#### **TB Case Definition Endpoint #3**

All individuals who are placed on anti-tuberculosis therapy with the intent of treating tuberculosis, regardless of whether or not they have met the above efficacy endpoint #1 or #2, are considered to have met this exploratory tuberculosis endpoint #3.

The TB endpoint definitions will be applied both to those subjects investigated for TB by the clinical site, and to those subjects who receive a clinical diagnosis of TB disease as part of routine care in other health facilities.

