### 7.3.2 Efficacy of MVA85A/AERAS-485

For the protocol-specified secondary objective of TB disease, subjects will be evaluated for the development of TB disease throughout the study utilizing TB Case Definition Endpoint #1 as the primary disease endpoint assessment. Less stringent TB case definitions, Endpoint #2 and Endpoint #3, will also be evaluated with no adjustment for multiplicity performed; it is acknowledged that the overall Type I error probability is not controlled in the evaluation of these endpoints.

The incidence of TB disease will be calculated as the number of new cases of TB disease in the PP population with a date of diagnosis from 28 days post-Study Day 0 vaccination through the end of study follow-up (as defined for each subject), divided by the total person-time of observation. Person-time observation will be calculated based on subject date of last contact with the study minus the date of Study Day 0 vaccination; sensitivity analyses will be performed to examine time at risk of TB based on INH treatment.

The primary statistical method to be used in the analysis of TB Case Definition Endpoints #1-3 will be vaccine efficacy (VE), estimated as 1-estimated hazard ratio, based on a Cox regression analysis of time to event for each Endpoint utilizing a model containing treatment group, ART status, and study site, performed on the PP population.

Time (months) to initial TB diagnosis for each Endpoint #1, #2 and #3 from Study Day 0 vaccination in each treatment group will be examined using the Kaplan-Meier estimate of the survival function, based on the PP population. Kaplan-Meier curves will be displayed by ART status and treatment group, over time (months) in study (time from Study Day 0 vaccination) to event. Summaries of median time (in months) to initial TB diagnosis and associated two-sided 95% confidence intervals will also be presented for each case definition endpoint. Time to initial diagnosis for each case definition endpoint will be compared using a two-sided log-rank test, stratified by study site and ART status at baseline. As a supportive analysis, the exact binomial (Clopper-Pearson) method will also be used to estimate VE and its corresponding two-sided 95% confidence interval conditional on the total number of events, and corresponding p-value, for each case definition Endpoint. All summaries will be presented by ART status and treatment group for subjects in the PP population.

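### Endpoint #2 counts an acid-fast-positive sterile-site specimen as TB even if culture grows a non-tuberculous mycobacterium, and the less stringent Endpoint #3 leaves out confirmed TB that is never treated

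*Protocol*

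**What the plan says.** Section 7.3.1 of the protocol sets three TB case definitions.

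- **Endpoint #1** is met by isolation or molecular identification of *M. tuberculosis*, by histopathology diagnostic for TB, or by a choroidal tubercle.
- **Endpoint #2** repeats those four categories and adds two based on acid-fast staining. The combination rule is "Any of the following numerical categories", so each category is enough alone. Category 5 reads in full: "A single smear/histology specimen positive for acid-fast bacilli from a normally sterile body site". Category 6 asks for two positive pulmonary or gastric smears "that are not found to be non-tuberculous mycobacteria bacteria on culture", plus a compatible radiographic or clinical feature.
- **Endpoint #3** takes in "All individuals who are placed on anti-tuberculosis therapy with the intent of treating tuberculosis", and does so "regardless of whether or not they have met the above efficacy endpoint #1 or #2".

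Section 7.3.2 makes Endpoint #1 the main disease endpoint and then says: "Less stringent TB case definitions, Endpoint #2 and Endpoint #3, will also be evaluated with no adjustment for multiplicity performed". Cox-based vaccine efficacy (VE), Kaplan-Meier curves, a log-rank test and an exact VE interval are planned for each of the three.

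**The concern.** Acid-fast staining shows a mycobacterium, not which species. Category 6 recognises this and lets culture overrule the smear. Category 5 rests on the same kind of evidence, needs only one specimen and no supporting feature, and has no such override. Section 3.6.3 foresees lumbar puncture, fine-needle aspiration, pleural biopsy and pericardial tap, so such specimens will arise. An NTM infection counted as TB is not the outcome named in the efficacy objective. If the vaccine does not act on it, it pulls estimated VE towards zero.

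For Endpoint #3, the label and the rule disagree. A reader told that #3 is less stringent than #1 will expect every #1 case to be in it. A subject with confirmed TB who never starts treatment is in #1 and #2 and is a non-event in #3. Some of these cases will be fatal ones, so what is missing from #3 need not be mild disease.

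**Working it through.** The protocol states no figure for misclassification, so there is none to reproduce. The first three steps are logical; the fourth is an illustration.

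**1. Endpoint #2, the two acid-fast categories side by side**

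| | Category 5 | Category 6 |
|---|---|---|
| Specimen | One, sterile site | Two, pulmonary or gastric |
| Supporting feature needed | No | Yes |
| Dropped if culture shows NTM | No | Yes |

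Take a lymph-node aspirate that is acid-fast positive and grows *M. avium*. Categories 1 to 4 and 6 are not met. Category 5 is met, and one category suffices. Result: an Endpoint #2 case.

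**2. Endpoint #3, two subjects**

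| Subject | #1 | #2 | #3 |
|---|---|---|---|
| Culture-positive, treated for TB | Yes | Yes | Yes |
| Culture-positive, dies or is lost before treatment | Yes | Yes | No |

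Section 3.6.3 has ways of finding the second subject: post-mortem examination where feasible, and matching of public laboratory smear and culture records to the study database.

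**3. Is either point repaired elsewhere?** The rest of the protocol has no species rule for category 5, no adjudication step and no second route into Endpoint #3.

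**4. Illustration of size.** Inputs from section 7.6: 325 per arm, control rate 2.0% or 1.5% per year for Endpoint #1, VE 70%, 21 months of accrual within 36 months, 2% per year death and loss. Assuming exponential times and uniform accrual, with λ the event rate, η = 0.02, s = λ + η, R = 1.75 and F = 3 years:

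events per arm = 325 × (λ/s) × [1 − (e^(−s(F−R)) − e^(−sF)) / (sR)]

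- Control, λ = 0.02: 325 × 0.5 × [1 − (0.9512 − 0.8869)/0.07] = 13.2.
- Vaccine, λ = 0.006: 325 × 0.2308 × [1 − (0.9680 − 0.9250)/0.0455] = 4.0 (unrounded exponentials).
- At 1.5% per year the same formula gives 9.96 and 3.02.

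As a check on the base, 17.2 events give one-sided power at 0.10 of 80% (log hazard ratio with variance 1/d0 + 1/d1), 83% (Freedman) or 89% (Schoenfeld), against 81% stated. The base is of the right order.

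Now add k NTM cases to each arm. The values of k are assumptions.

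apparent VE = 1 − (vaccine + k)/(control + k)

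| k per arm | 2.0% per year | 1.5% per year |
|---|---|---|
| 0 | 1 − 4.03/13.21 = 70% | 1 − 3.02/9.96 = 70% |
| 1 | 1 − 5.03/14.21 = 65% | 1 − 4.02/10.96 = 63% |
| 2 | 1 − 6.03/15.21 = 60% | 1 − 5.02/11.96 = 58% |

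These counts are for Endpoint #1. Endpoint #2 contains every #1 category and two more, so its true-TB base is at least as large. If VE is the same for the added cases, the dilution in #2 is at most what the table shows.

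For Endpoint #3, if an equal share of confirmed cases in both arms goes untreated, the ratio of arms does not change but events are lost. On the same base, shares of 5%, 10% and 20% (assumed) leave 16.4, 15.5 and 13.8 of 17.2 events, and Freedman power falls from 83% to 81.5%, 80% and 76%. Since #3 also admits treated cases without confirmation, the proportional loss there would be smaller.

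**The case against.** The strongest reply is that little of consequence is touched. Efficacy is a secondary objective, Endpoint #1 contains neither category 5 nor a treatment condition, and section 7.3.2 already disclaims type I error control for #2 and #3. This stands, and it limits the weight of the point.

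On Endpoint #3, section 7.3.1 calls it exploratory, and less stringent may refer only to the diagnostic evidence required. A reader might infer that the protocol promises nested endpoints, or a graded robustness check, and breaks that promise. It makes no such promise, and untreated confirmed cases still count in #1 and #2. What remains is that the label invites a reading that the rule does not support.

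A reader might also extend the complaint to histopathology, which has no culture override in #1 or #2. That does not hold. The category reads "Histopathology diagnostic for tuberculosis disease (such as caseating granulomas"), so the histology must already be diagnostic for TB, and granulomas are only an example.

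NTM disease may be rare here. Entry requires two CD4 counts above 350, or above 300 on ART with undetectable viral load (section 3.2.3), and AIDS-defining illness is excluded (section 3.2.4). The infections class in supplementary Table S2 lists no NTM event among 649 subjects, although it covers serious events only. Dilution is also not certain, because section 1.1 describes Ag85A as highly conserved across mycobacterial species. Both remarks bear on size, not on the rule.

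Finally, a statistical analysis plan might settle discordant smear and culture results. But section 7.3.1 fixes the case definitions itself and defers nothing, whereas section 7.1 expressly defers major deviations. A later plan that excluded NTM from category 5 would be changing the protocol's definition.

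**Conclusion.** Both parts hold as readings of the current text. Category 5 of Endpoint #2 classifies a sterile-site specimen shown to be NTM as TB, against the safeguard in category 6. Endpoint #3 is not a superset of #1 and #2, because it omits culture- or molecularly-confirmed TB in subjects who die or are lost before treatment.

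The effect is confined to the two supplementary endpoints. A reader might infer that the main efficacy result is biased, or that VE for #2 will be diluted by 5 to 10 points. Neither follows: Endpoint #1 is untouched, and the documents give no rate of NTM or of untreated confirmed TB. The movement from about 70% to 65% or 60% assumes one or two NTM cases per arm, no vaccine effect on NTM, and the Endpoint #1 event base, which makes it an upper bound for #2. It shows only that, with about 17 expected events, one or two misclassified subjects per arm would be visible in the estimate.

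**What to change.** - **Endpoint #2, category 5:** add a condition that the specimen has not been found to be non-tuberculous mycobacteria on culture or molecular identification. As in category 6, a specimen never speciated stays a case, and a subject with *M. tuberculosis* from another site still qualifies through category 1 or 2.
- **Endpoint #3:** define it as meeting Endpoint #1 or #2, or starting treatment for TB as now worded, dated at the earliest qualifying event. At minimum, stop describing it as a less stringent version of #1.
- Make the two changes together. If #3 absorbs #2 while category 5 stays as it is, NTM cases enter #3 as well.
- Leave the histopathology category of #1 and #2 unchanged.

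The cost is two phrases in section 7.3.1 and the matching programming. No new tests are needed, since culture and treatment information is already gathered. The downside is that a case may leave #2 or be added to #3.

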#### **TB Case Definition Endpoint #3**

All individuals who are placed on anti-tuberculosis therapy with the intent of treating tuberculosis, regardless of whether or not they have met the above efficacy endpoint #1 or #2, are considered to have met this exploratory tuberculosis endpoint #3.

The TB endpoint definitions will be applied both to those subjects investigated for TB by the clinical site, and to those subjects who receive a clinical diagnosis of TB disease as part of routine care in other health facilities.

### 7.3.2 Efficacy of MVA85A/AERAS-485

For the protocol-specified secondary objective of TB disease, subjects will be evaluated for the development of TB disease throughout the study utilizing TB Case Definition Endpoint #1 as the primary disease endpoint assessment. Less stringent TB case definitions, Endpoint #2 and Endpoint #3, will also be evaluated with no adjustment for multiplicity performed; it is acknowledged that the overall Type I error probability is not controlled in the evaluation of these endpoints.

The incidence of TB disease will be calculated as the number of new cases of TB disease in the PP population with a date of diagnosis from 28 days post-Study Day 0 vaccination through the end of study follow-up (as defined for each subject), divided by the total person-time of observation. Person-time observation will be calculated based on subject date of last contact with the study minus the date of Study Day 0 vaccination; sensitivity analyses will be performed to examine time at risk of TB based on INH treatment.

The primary statistical method to be used in the analysis of TB Case Definition Endpoints #1-3 will be vaccine efficacy (VE), estimated as 1-estimated hazard ratio, based on a Cox regression analysis of time to event for each Endpoint utilizing a model containing treatment group, ART status, and study site, performed on the PP population.

Time (months) to initial TB diagnosis for each Endpoint #1, #2 and #3 from Study Day 0 vaccination in each treatment group will be examined using the Kaplan-Meier estimate of the survival function, based on the PP population. Kaplan-Meier curves will be displayed by ART status and treatment group, over time (months) in study (time from Study Day 0 vaccination) to event. Summaries of median time (in months) to initial TB diagnosis and associated two-sided 95% confidence intervals will also be presented for each case definition endpoint. Time to initial diagnosis for each case definition endpoint will be compared using a two-sided log-rank test, stratified by study site and ART status at baseline. As a supportive analysis, the exact binomial (Clopper-Pearson) method will also be used to estimate VE and its corresponding two-sided 95% confidence interval conditional on the total number of events, and corresponding p-value, for each case definition Endpoint. All summaries will be presented by ART status and treatment group for subjects in the PP population.

Efficacy of MVA85A/AERAS-485 in the prevention of TB disease will be examined for all subjects in the PP population receiving ART at baseline compared to subjects receiving ART at baseline but who receive placebo (secondary objective #3), as described above for secondary objective #1.

In this proof-of-concept study, variables related to HIV status and infection status such as baseline QFN status which may impact development of TB disease may also be included in further stratified Cox proportional hazards regression models, to explore differences between treatment groups in the incidence of TB disease, given proportional hazards assumptions. In addition, the efficacy of MVA85A/AERAS-485 in the prevention of TB disease will be examined for all subjects in the PP population receiving MVA85A/AERAS-485 and isoniazid

preventative therapy at any time during the study following Study Day 0 vaccination compared to subjects receive placebo (secondary objective #4).

Adjustment to time at risk based on start of isoniazid (INH) therapy and examination of cases which occur within 24 months following Study Day 28 (28 days post-Study Day 0 vaccination) will be examined as supportive analyses. Results will be summarized by ART status at baseline, treatment group and study site, as appropriate. Supportive analyses will also be performed based on the ITT population and all randomized subjects' populations. Sensitivity analyses including examination of subjects put on ART during the study and missing data imputations will be explored.

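### The TB incidence rate in Section 7.3.2 counts cases from Day 28 but person-time from Day 0 to last contact, so reported rates come out about 4–6% too low; the reach of the Day-28 window is also left unstated

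*Protocol*

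**What the plan says.** All the relevant text is in Section 7.3.2 of the protocol.

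- **Numerator of the incidence.** New cases in the per-protocol population "with a date of diagnosis from 28 days post-Study Day 0 vaccination through the end of study follow-up".
- **Denominator.** "Person-time observation will be calculated based on subject date of last contact with the study minus the date of Study Day 0 vaccination". The only adjustment of time at risk that the section names is for isoniazid treatment.
- **Primary efficacy method.** One minus the hazard ratio from this model: "based on a Cox regression analysis of time to event for each Endpoint utilizing a model containing treatment group, ART status, and study site". No case window is repeated here.
- **Kaplan-Meier and log-rank.** "Time (months) to initial TB diagnosis for each Endpoint #1, #2 and #3 from Study Day 0 vaccination in each treatment group" is the time variable. No case window is repeated here either.
- **Supportive exact method.** An efficacy estimate "conditional on the total number of events, and corresponding p-value, for each case definition Endpoint", again with no window.
- **A supportive analysis anchored at Day 28.** "examination of cases which occur within 24 months following Study Day 28 (28 days post-Study Day 0 vaccination".

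Two other places matter. Section 3.6.6 keeps every vaccinated subject in follow-up unless consent is withdrawn, so a TB diagnosis does not end contact. The three case definitions in Section 7.3.1 carry no time window of their own.

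**The concern.** An incidence rate needs the same window above and below the line. Here the two differ at both ends. At the start, each subject contributes 28 days in which a diagnosis would not be counted. At the end, a subject who has become a case, and can no longer become a new one, goes on contributing time. Both faults push the rate down. The first acts almost equally in the two arms. The second acts more in the arm with more cases, so it also moves the rate ratio slightly towards one.

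The second matter is one of clarity. The Day-28 window is attached to the incidence and to one supportive analysis. It is not attached to the Cox, Kaplan-Meier, log-rank or exact analyses. With about 13 to 19 events expected, whether a diagnosis on Day 15 counts in the efficacy estimate should be settled before unblinding.

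**Working it through.** **Stated figures.** The protocol gives no person-time total and no expected incidence result. The only stated figures built on the same inputs are the powers in Section 7.6: 81%, 71%, 67% and 57%. On those inputs Freedman's formula gives 83.0%, 74.5%, 71.4% and 62.6%. The stated powers are not reproduced but lie on the cautious side, and this does not bear on the point.

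**Inputs (Section 7.6).** Control incidence λ of 2.0% or 1.5% per year; efficacy 70% or 60%; n = 325 per arm; enrolment over 21 months with follow-up from 15 to 36 months, taken as uniform, so τ runs from 1.25 to 3 years; death and loss η = 2% per year. The excluded period is d = 28/365.25 = 0.0767 year. Assumptions: constant hazards, and cases that stay in contact after diagnosis at the same rate as other subjects.

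**Denominator as written.** Mean time to last contact is the average over τ of (1 − e^(−ητ))/η = 24.94 months. For 325 subjects that is 675.4 person-years, whatever the TB rate.

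**Matching denominator.** With k = λ + η, time from Day 28 to the earliest of diagnosis, loss or study end is the average over τ of (e^(−kd) − e^(−kτ))/k. Cases from Day 28 equal λ times this, so the matched rate is λ itself and the relative error is 1 − matched/675.4.

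| Arm rate per year | Matched person-years | Cases from Day 28 | Rate as written, per 100 | Too low by |
|---|---|---|---|---|
| 2.0% (control) | 635.7 | 12.71 | 1.883 | 5.9% |
| 1.5% (control) | 639.3 | 9.59 | 1.420 | 5.3% |
| 0.8% (vaccine, 60% of 2.0% prevented) | 644.5 | 5.16 | 0.763 | 4.6% |
| 0.6% (vaccine, 70% of 2.0% or 60% of 1.5% prevented) | 646.0 | 3.88 | 0.574 | 4.3% |
| 0.45% (vaccine, 70% of 1.5% prevented) | 647.1 | 2.91 | 0.431 | 4.2% |

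**Split of the error.** The 28 days are 0.92 of 24.94 months, or 3.7%, in each arm. Failure to stop at diagnosis supplies the rest: 1.6–2.2% in control and 0.5–0.9% in vaccine.

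**Effect on a crude rate ratio.** At 70% efficacy: 0.574/1.883 = 0.305 and 0.431/1.420 = 0.304, so efficacy reads 69.5–69.6%. At 60%: 0.763/1.883 = 0.405 and 0.574/1.420 = 0.404, so efficacy reads a little under 60%, by about half a point.

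**Sensitivity to follow-up.** With 12 to 33 months the rates are 4.6–6.1% too low. Section 2.2 guarantees only 6 months after a booster given at 6–9 months. If every subject had only 12–15 months, the error would be 6.5–8.7%.

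**Cases before Day 28, both arms together.** Expected number = 325 × (λ control + λ vaccine) × 28/365.

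- 2.0%, efficacy 70%: 325 × 0.026 × 0.0767 = 0.65, of 17.2 events, 3.8%.
- 2.0%, efficacy 60%: 325 × 0.028 × 0.0767 = 0.70, of 18.6 events, 3.8%.
- 1.5%, efficacy 70%: 325 × 0.0195 × 0.0767 = 0.49, of 13.0 events, 3.7%.
- 1.5%, efficacy 60%: 325 × 0.021 × 0.0767 = 0.52, of 14.0 events, 3.7%.

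**The case against.** The strongest reply is that nothing important changes. The primary efficacy estimate is one minus a Cox hazard ratio, and neither it nor the log-rank test uses this person-time. Time to initial diagnosis already stops at the event in those methods. The crude rate-ratio efficacy that shifts by half a point is not an estimator the protocol names, and the shift is far inside sampling error with 13 to 19 events. Efficacy is a secondary objective. All of this stands, and it sets the severity.

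A second reply is that the analysis plan would settle when each subject's clock stops. This stands only in part. The protocol does not leave person-time open: it fixes a formula, and an analysis plan that follows it inherits the error.

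A reader might go further and infer that the methods do use different sets of cases. The text does not establish that. Starting the clock at Day 0 fixes the time origin, not which events count. If events count only from Day 28, the hazard ratio and the log-rank statistic are the same whether the clock starts on Day 0 or Day 28. The section states the window once and then lists the methods without repeating it; the Study Abstract gives the same window for all three endpoints, and one supportive analysis is anchored at Day 28. The sponsor may well have meant the window to apply throughout. What can be said is that the text is silent and that its literal reading leaves the window out.

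A reader might also put the early cases at about one, or 6% of events. That applies the control rate to all 650 subjects (650 × 0.02 × 28/365 = 1.0) but divides by the 17.2 events expected at 70% efficacy. On a single scenario the share is about 4%. Nor do the documents give a figure for undiagnosed TB at entry that would raise it; Section 3.2.4 excludes any evidence of active TB, and screening includes a chest x-ray.

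**Conclusion.** The incidence formula is wrong as stated. On the planning inputs of Section 7.6 it understates the TB rates by 5.3–5.9% in control and 4.2–4.6% in vaccine, of which 3.7% comes from the 28 days. The part due to time after diagnosis assumes that cases remain in contact, as Section 3.6.6 provides; earlier death or loss among cases would make it smaller. Shorter follow-up would make the 28-day part larger.

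The reach of the Day-28 window is an ambiguity rather than a demonstrated conflict. Its expected weight is 0.5–0.7 of a case.

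It would be wrong to conclude that the efficacy result is biased: no test, decision or safety result depends on this person-time. The severity is minor. The reported rates are nevertheless descriptive results that others may use, and the correction is simple.

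**What to change.** Change two sentences in Section 7.3.2.

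1. Define person-time for the per-protocol incidence, for each endpoint, as running from Day 28 after the first vaccination to the earliest of first qualifying TB diagnosis, death or last contact. Subjects whose diagnosis, death or last contact falls before Day 28 then contribute no person-time.
2. State that the same Day-28 case window applies to the Cox, Kaplan-Meier, log-rank and exact per-protocol analyses.

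How the supportive intent-to-treat analysis treats early cases is a matter of choice and is not part of this correction. The change needs no new data and no change to visits or sample size. It should be made before unblinding, so that the handling of any early case is not decided with the results in view.
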